### Transcranial direct current stimulation

2.5

Homeostatic plasticity will be examined through a priming-test approach, where priming stimuli will induce and test stimuli will capture the homeostatic response (14). Previous research (28) has suggested that the fidelity of homeostatic response occurs when the prime protocol does not lead to noticeable changes in basal synaptic transmission. And prior studies (29) in mice models have demonstrated that anodal tDCS-induced LTP does not impact the efficiency of basal synaptic transmission. Therefore, tDCS is deemed the most suitable priming method, this study will also employ tDCS to trigger a homeostatic response. Given that the regulation of homeostatic plasticity involved both upward (30) and downward (31) homeostasis, anodal and cathodal tDCS were going to be used to prime upward and downward homeostasis, respectively. Sham tDCS was intended to serve as a control to evaluate the success of the priming process.

Continuous tDCS will be conducted using a DC stimulator. A steady 1 mA current will be delivered via wet sponge electrodes (7 cm × 5 cm) placed on the left M1 region and the right contralateral supraorbital area. The tDCS polarity will be determined by the electrode on the left M1. In the case of sham tDCS, only a small current pulse will occur every 550 ms (110 μA over 15 ms) instead of the actual stimulation current. The peak current will last for 3 ms, creating a brief skin sensation similar to real tDCS but lacking therapeutic benefits. To ensure the double-blind procedure, the real and sham stimulation will be managed by the code linked to the DC stimulator. Before each stimulation session, the researcher will receive the code of the session (unaware of the type of stimulation), and will start the stimulation by inputting the code to activate the DC stimulator.

### Transcranial magnetic stimulation

2.6

Due to the specificity of these patients, intermittent theta burst stimulation (iTBS) will be utilized in this study to prevent fatigue from prolonged testing. Previous research (32) has proposed that iTBS, as opposed to conventional repetitive TMS, can expedite changes in neural activity while maintaining clinical effectiveness.

Both single-pulse TMS and iTBS will employ a rapid stimulator and a standard figure-of-eight coil. The coil will be placed tangentially on the scalp, with the handle angled 45° from the midline. TMS will be consistently applied over the optimal site (hotspot) to evoke the largest MEP in the relaxed right first dorsal interosseus (FDI) muscle. The individual resting motor threshold (RMT) will be evaluated, and the effects following transcranial stimulation will be explored using single-pulse TMS. RMT will be defined (33) as the minimal stimulation intensity required to generate a TMS-induced MEP peak-to-peak amplitude of ≥50 μV in at least half of the 10 consecutive trials. The iTBS pattern will comprise sets of bursts of 3 pulses at 50 Hz repeated at 5 Hz; a 2 s train of TBS will be delivered every 10 s for a total of 192 s (600 pulses). The stimulation intensity will be set at 90% of the individual RMT.

### Cortical excitability measurements

2.7

This study will evaluate the cortical excitability of the motor cortex at four time points: BASELINE, INTER, POST1, and POST2, to investigate if priming stimuli induce and test stimuli capture the homeostatic response. Single-pulse TMS will be utilized to stimulate the motor cortex and generate MEPs in the peripheral muscles. The amplitude of these MEPs will indicate motor cortical excitability. We will administer 10 single-pulse TMS (stimulation intensity: 120%RMT; time interval: 5 s) to target the left M1 at four time points. Motor cortex excitability will be represented by averaging the peak-to-peak amplitudes of MEPs induced on the FDI muscle of the right hand, recorded during the experiment. The FDI muscle will be chosen for its small, localized, and palpable nature (34). MEPs will be recorded using the Ag-AgCl surface electrode provided with the TMS device. The EMG signal will undergo filtering and digitization using an analog–digital converter, then will be processed with low-pass, high-pass, and 50 Hz-Notch-Filter before being storage in a personal computer for offline analysis.

### Behavioral assessments

2.8

The level of consciousness of DoC patients will be evaluated using the CRS-R, which consists of six subscales with a total of 23 items (35). The patients’ consciousness level will be evaluated across six dimensions: auditory, visual, motor, oromotor/verbal, communication and arousal. Comparing the total score, the best score of each subscale can more accurately reflect the patient’s condition. Due to the fluctuating consciousness levels in these patients, we will select the best of five assessments over a 10-day period to represent the patient’s baseline consciousness level. In each session, considering the limited duration of post-effects induced by transcranial stimulation, CRS-R evaluations will be conducted before and after stimulation, focusing on specific items, including the best items from each subscale at baseline and those that are one level above or below the best items. The scores of these specific items will be used to assess whether each session had a behavioral impact on the patient’s consciousness. Patients will undergo reassessment using CRS-R at 3, 6, and 12 months after the conclusion of the trial to collect prognostic data.

It’s worth noting that, in addition to DoC, there are various conditions associated with impaired levels of consciousness. The clinical symptoms of these conditions are summarized in Table 2.

**Table 2 tab2:** Symptoms associated with consciousness states.

State	Consciousness level	Clinical features and manifestations
Alertness/Wakefulness	Full	Full environmental attention; Normal conversation and behavior; Intact orientation; Appropriate responses to all stimuli
Somnolence	Mild impairment	Decreased attention; Slowed responses; Easily arousable; Normal response to strong stimuli
Lethargy	Moderate impairment	Delayed responses; Slurred speech; Requires repeated stimulation; Limited environmental interaction
Stupor	Severe impairment	Responds only to vigorous stimulation; Unable to maintain wakefulness; Minimal verbal response; Limited to pain responses
Coma	Complete loss	Unarousable; No spontaneous behavior; Only reflexive responses; No sleep–wake cycle
Akinetic Mutism	Partially preserved	Eyes open with preserved wakefulness; No spontaneous speech/movement; Limited environmental response; Preserved arousal mechanisms
Apallic Syndrome	Extremely severe impairment	Decorticate posturing; Preserved sleep–wake cycles; No purposeful behavior; Primitive reflexes only
Unresponsive Wakefulness Syndrome	Extremely severe impairment	Preserved sleep–wake cycle; No purposeful behavior; Reflexive responses only; No cognitive function
Minimally Conscious State	Severely impaired with partial preservation	Intermittent purposeful behavior; Basic command following; Inconsistent but reproducible responses
Locked-in Syndrome	Fully preserved	Preserved consciousness; Complete paralysis except eye movement; Intact cognition; Communication through eye movements
Delirium	Fluctuating impairment	Fluctuating attention and awareness; Disorientation; Perceptual disturbances; Unstable behavioral patterns
Catatonia	Variable	Abnormal motor behavior; Fixed posturing; Variable responsiveness; Possible excitement or stupor

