### Procedures

2.4

The study process will begin as early as 28 days after the patient’s injury, and the entire experimental process will be finished within 10 days. After informing the patient’s legal representative about the experimental content and potential adverse reactions, written informed consent will be obtained from them. They will be advised that they can choose to exit the study at any time without the requirement for providing a reason. After informing the healthy subjects of the experimental content and potential adverse reactions, they will sign the informed consent form.

Before the trial, DoC patients will have the option to undergo a functional magnetic resonance imaging (fMRI) scan, and they can choose to decline. Over a period of 10 days, five CRS-R assessments, and an fMRI scan will be completed. The study protocol is a repeated-measures crossover design. According to different tDCS priming protocols (anode, cathode, sham), the trial will be divided into three distinct sessions. Each session will involve 10 min of tDCS priming followed by 192 s of TMS test, with both transcranial stimulations specifically targeted toward the left M1. We will measure the motor evoked potential (MEP) amplitude at four time points: baseline (PRE), after tDCS (INTER), and at 5 and 15 min following TMS (POST-1, POST-2). CRS-R data will be collected at baseline (PRE) and 20 min after TMS (POST-3). Upon enrollment, participants will receive a serial number based on their order of enrollment, with each serial number corresponding to a randomly generated session order. Subjects will then undergo three sessions following the designated session order, with a two-day washout period between each session. The entire trial will be completed in 5 days. Patient prognostic data will be gathered at 3, 6, and 12 months after the conclusion of the study. Figure 1 provides a detailed illustration of the study flow.

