### Statistical analysis

2.11

A single transcranial stimulation typically leads to limited behavioral improvement but increases cortical excitability due to its immediate effects (36). Therefore, the primary focus of this study will be to analyze the trend of MEP changes over time in different priming types, comparing healthy individuals with DoC patients. At the individual level, the cathodal tDCS group will be compared with the sham group. The primary outcome of this study will be MEP, a measure used to assess neurophysiological changes. Since the baseline MEP in each session will be influenced by various factors such as the individual’s daily state, MEP data from different sessions will lack comparability. Therefore, all MEP data will be normalized in this study (normalized MEP = MEP/MEP baseline). The normalized MEP data will be subjected to an analysis of variance (ANOVA) to explore the retention of homeostatic plasticity in DoC patients and to determine whether the combination of cathodal tDCS and iTBS is superior to iTBS alone.

While a single stimulus may not directly lead to a change in behavior, this study will conduct a CRS-R assessment (specific item) before and after each session to ensure that any potential improvements are not overlooked. Homeostatic plasticity, as a fundamental characteristic of synapses, can impact a range of synaptic activities and may even influence levels of consciousness and prognosis. Therefore, the CRS-R score, which assesses the level of consciousness, will be considered as a secondary outcome of this study.

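### A before/after CRS-R change within one session cannot show that session's behavioural impact; only the contrast with the sham-priming session is controlled, and it is not stated for CRS-R

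*Protocol article*

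**What the plan says.** On the content of sessions, section 2.4 states: "According to different tDCS priming protocols (anode, cathode, sham), the trial will be divided into three distinct sessions". It continues: "Each session will involve 10 min of tDCS priming followed by 192 s of TMS test". Section 2.6 identifies the TMS test as iTBS of 600 pulses, with the same pattern and relative intensity throughout. Section 2.5 gives the role of the sham: "Sham tDCS was intended to serve as a control to evaluate the success of the priming process". Only the tDCS is shammed.

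On CRS-R, section 2.4 sets one assessment at PRE and one at POST-3, 20 minutes after TMS. Section 2.8 says that the item scores from these assessments "will be used to assess whether each session had a behavioral impact on the patient". Section 2.11 ranks CRS-R as a secondary outcome and explains that it is taken before and after each session "to ensure that any potential improvements are not overlooked".

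On fluctuation, section 2.8 states: "Due to the fluctuating consciousness levels in these patients, we will select the best of five assessments over a 10-day period". That safeguard serves the pre-trial baseline. Within a session there is a single assessment on each side of stimulation.

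On comparisons, section 2.11 names cathodal tDCS against sham, and the combination of cathodal tDCS and iTBS against iTBS alone. Both appear in the paragraph on normalized MEP. The CRS-R paragraph that follows mentions only assessment before and after each session.

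**The concern.** The stated target is the impact of each session, and the stated measurement is a before/after change in that session. With active iTBS in all three sessions, no session shows what CRS-R would do over the same interval without stimulation. A rise could come from the iTBS, the tDCS, repeat testing of the same items, arousal from handling and stimulation, or spontaneous fluctuation.

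At stake is how a secondary outcome may be interpreted. Taken literally, section 2.8 would let a rise after any session, including sham tDCS plus iTBS, be described as a behavioural effect of that session. No later choice of analysis can recover that quantity from these data. The quantity that can be recovered, the effect of priming given iTBS, is not the one named.

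**Working it through.** The protocol states no figure on this point, so there is none to reproduce. The check has two parts: what the design can identify, and an illustration of the consequence.

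**Identification.** For one patient, write the PRE-to-POST-3 CRS-R change as follows, where B is the iTBS effect, P_a and P_c are the effects of anodal and cathodal priming given that iTBS follows, and N is everything else that shifts the score (retest, arousal, time):

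- sham tDCS + iTBS: B + N + noise
- cathodal tDCS + iTBS: B + P_c + N + noise
- anodal tDCS + iTBS: B + P_a + N + noise

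B and N appear together in every line, so no combination of the three sessions separates them. The differences do isolate priming:

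- cathodal minus sham: (B + P_c + N) − (B + N) = P_c
- anodal minus sham: (B + P_a + N) − (B + N) = P_a

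This needs N to be the same on average across sessions, which randomized session order supports, and carry-over to be negligible.

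The interval over which N can act is at least 10 min + 192 s (3.2 min) + 20 min = 33.2 min, from the times in section 2.4.

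**Illustration.** Inputs from the document: 30 patients (15 MCS + 15 UWS, section 2.2), three sessions (section 2.4), significance level 0.05 (section 2.11). Assumed, because the document does not give them: an SD of the session CRS-R change of 1, 1.5 or 2 points; a systematic drift of 0, 0.25, 0.5 or 1 point common to all sessions; normal and independent noise. There is no stimulation effect of any kind. For each combination 20,000 trials were simulated and tested with a two-sided paired t-test (29 df, critical value 2.0452). Ranges are over the three SDs.

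| Drift (points) | False positive, one session before/after | At least one of three sessions | Cathodal-minus-sham contrast |
|---|---|---|---|
| 0 | 4.8% to 5.2% | 14.3% to 14.6% | 5.0% to 5.2% |
| 0.25 | 10.5% to 26.4% | 27.3% to 61.1% | 4.8% to 5.0% |
| 0.5 | 25.8% to 76.2% | 59.6% to 98.5% | 5.1% |
| 1.0 | 75.5% to 99.9% | 98.7% to 100% | 4.9% |

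The zero-drift figure for three sessions agrees with 1 − (1 − 0.05)^3 = 1 − 0.857 = 14.3%. The contrast holds its level because a drift shared by all sessions cancels, as the algebra shows. The table does not say how large the drift is in these patients.

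**The case against.** The strongest reply is that the article states no within-session test, responder rule or threshold for CRS-R. The sentence in section 2.8 can be read as measuring before and after in every session and then comparing sessions, with the detail left to a fuller document. The trial is a randomized, double-blind crossover, and sham tDCS plus iTBS is its declared control for priming. iTBS is the probe that captures the homeostatic response, so the absence of sham iTBS is no flaw for the main question. CRS-R is secondary, and section 2.11 itself expects little behavioural change from a single stimulation.

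Much of this stands, and it rules out several stronger readings that a reader might infer:

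- That fluctuation will be reported as an effect. No decision rule says so. Fluctuation that averages to zero leaves a group-level test at about 5% per session; larger error needs drift, several unadjusted tests or patient-by-patient reading. A count of falsely responding patients would need a responder rule that the protocol does not contain.
- That the trial has no comparator. It has a valid one for priming.
- That a false CRS-R signal would drive the sequential-stimulation proposal in the Discussion. That proposal is for patients with preserved homeostatic regulation, which section 2.11 defines by MEP.
- That the shortened item list hides improvement. A gain of two levels would ordinarily still register as a gain, with only its size capped, and section 2.8 gives a reason for the short list.

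Nor could the five pre-enrolment assessments serve as the noise reference within a session: they are spread over 10 days, whereas the interval in question is about half an hour.

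What the reply does not remove is the stated target. The article names the impact of each session, which the design cannot identify, and gives the controlled comparison for MEP but not for CRS-R. That is a matter of what is claimed, not of omitted detail.

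**Conclusion.** The point holds in a limited form. The use of session CRS-R scores set out in section 2.8 asks for something that three sessions with identical active iTBS cannot supply. The between-session contrast of changes is available from data already planned and answers a narrower question, the effect of priming given iTBS.

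The identification argument rests only on the session content in sections 2.4 to 2.6 and needs no assumed number. The error rates are illustrative and depend on the assumed SD and drift: with no drift a single within-session test is sound at group level as a test of mean change, though even a real mean change could not be attributed to stimulation. The consequence is confined to a secondary outcome; the primary MEP analysis is not affected.

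**What to change.** In sections 2.8 and 2.11, and in any analysis plan:

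- Define the session CRS-R secondary outcome as the within-patient difference in PRE-to-POST-3 change, cathodal minus sham priming and anodal minus sham priming.
- Limit the behavioural claim to an effect of priming when iTBS follows.
- State that the impact of iTBS, or of a whole session (including sham tDCS plus iTBS), cannot be estimated, and that a before/after change in a single session is descriptive.

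This changes wording only: no new visits, assessments or patients. The cost is a narrower behavioural claim.

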### fMRI scan

2.9

Before commencing the experiment, T1 scans will be conducted to confirm the integrity of patients’ M1 are intact and that the motor cortex excitability can be detected using TMS-MEP. Resting state fMRI data will be gathered post-experiment for further analysis to explore neuroimaging differences between patients with and without homeostatic plasticity.

### Data safety and management

2.10

In addition to collecting behavioral, electrophysiological, and neuroimaging data, the researchers will also gather data from the case report forms (CRF). The study will store all electronic data in the Institute’s database and will securely store paper data in the Institute’s lockers. The identity of the subjects involved will be concealed when the above data is used for publication.

### Statistical analysis

2.11

A single transcranial stimulation typically leads to limited behavioral improvement but increases cortical excitability due to its immediate effects (36). Therefore, the primary focus of this study will be to analyze the trend of MEP changes over time in different priming types, comparing healthy individuals with DoC patients. At the individual level, the cathodal tDCS group will be compared with the sham group. The primary outcome of this study will be MEP, a measure used to assess neurophysiological changes. Since the baseline MEP in each session will be influenced by various factors such as the individual’s daily state, MEP data from different sessions will lack comparability. Therefore, all MEP data will be normalized in this study (normalized MEP = MEP/MEP baseline). The normalized MEP data will be subjected to an analysis of variance (ANOVA) to explore the retention of homeostatic plasticity in DoC patients and to determine whether the combination of cathodal tDCS and iTBS is superior to iTBS alone.

While a single stimulus may not directly lead to a change in behavior, this study will conduct a CRS-R assessment (specific item) before and after each session to ensure that any potential improvements are not overlooked. Homeostatic plasticity, as a fundamental characteristic of synapses, can impact a range of synaptic activities and may even influence levels of consciousness and prognosis. Therefore, the CRS-R score, which assesses the level of consciousness, will be considered as a secondary outcome of this study.

Patients will be categorized into subgroups based on consciousness levels and prognosis. For consciousness levels, patients will be classified into the MCS or UWS group based on the best result from five baseline CRS-R assessments, To classify a CRS-R record as reflecting MCS, the participant must achieve at least one of the following criteria: a score of 1 on the communication subscale (intentional but non-functional yes/no communication), a score of 3 or higher on the auditory subscale (command-following), a score of 2 or higher on the visual subscale (visual fixation or better), a score of 3 or higher on the motor subscale (localization to noxious stimulation or better), or a score of 3 on the oromotor/verbal subscale (intelligible verbalization). If none of these criteria are met, the CRS-R record will be classified as reflecting UWS (37). For prognosis, patients will be evaluated at 3, 6, and 12 months, with those showing an increase of over 11 Rasch units (approximately 4–6 CRS-R points) (38) classified as the good prognosis group, while others will be placed in the poor prognosis group. A preserved homeostatic plasticity response is defined as a significant modulation of MEP amplitude following the priming-test protocol, consistent with the sliding threshold theory of synaptic plasticity. Its preservation was further compared between the MCS and UWS groups, as well as between the good and poor prognosis groups.

In this study, statistical analysis will be conducted using IBM SPSS Statistics 26 software. The collected data will first undergo normal distribution testing via Kolmogorov–Smirnov tests. If the data meets the criteria for a normal distribution, a three-way repeated measures ANOVA will then be carried out. However, if the data does not adhere to a normal distribution, Friedman’s ANOVA will be utilized instead. Following a significant outcome from the ANOVA, two-way ANOVAs will be conducted within each group to explore temporal changes in mean MEP amplitude. Additionally, Pearson correlation will be used to examine the relationship between homeostatic plasticity retention, consciousness, and prognosis. A significance level of *p* < 0.05 will be employed for determining statistical significance.

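### Individual retention is defined by significance, but with one session per condition a single patient's data contain no session-level error term to test against

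*Protocol article*

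**What the plan says.** Four parts of the protocol article meet here.

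- **Sessions (2.4 Procedures).** "According to different tDCS priming protocols (anode, cathode, sham), the trial will be divided into three distinct sessions". Each participant thus has exactly one session per priming type. MEPs are taken at four points in each session: "baseline (PRE), after tDCS (INTER), and at 5 and 15 min following TMS (POST-1, POST-2").
- **Pulses (2.7 Cortical excitability measurements).** "We will administer 10 single-pulse TMS (stimulation intensity: 120%RMT; time interval: 5 s) to target the left M1 at four time points". The 10 amplitudes are averaged to one value per time point.
- **Normalisation and contrast (2.11 Statistical analysis).** Because baseline differs from session to session, every MEP is divided by its session's baseline. Then: "At the individual level, the cathodal tDCS group will be compared with the sham group".
- **Definition and use (2.11 and 2.9 fMRI scan).** "A preserved homeostatic plasticity response is defined as a significant modulation of MEP amplitude following the priming-test protocol", in line with sliding threshold theory, at p < 0.05. Preservation is then compared between MCS and UWS and between prognosis groups, and retention is correlated with consciousness and prognosis. The imaging analysis is to "explore neuroimaging differences between patients with and without homeostatic plasticity", which needs a status for each patient.

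**The concern.** A significance statement about one person needs an error term for that person's cathodal-minus-sham difference. What is randomised is the order of the sessions, so the condition is replicated only by repeating sessions, and no condition is repeated. Once the pulses are averaged, the comparison at each time point is one number against one number.

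The only replication left within a person is the pulses inside a block, or the two post-TMS blocks inside a session. Neither replicates the condition. All normalised values of a session share one divisor, so the sampling error of that baseline mean moves them together. Any change of state between the baseline and post blocks also moves all pulses of a block together. A test across pulses leaves both out of its error term.

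At stake is the make-up of the preserved group. If patients without a response enter it too often, the links to consciousness level, prognosis and imaging are diluted wherever they rest on the label.

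**Working it through.** **The plan's own figure.** The only design figure is 15 per group in section 2.3, for the group-level ANOVA (f = 0.3, 80% power, 5% alpha, 20% loss). A group-by-time interaction with three groups, three measurements and an assumed correlation of 0.3 needs 12 per group, and 12/0.8 = 15. An assumed correlation of 0.5 gives 9, and 9/0.8 = 11.25, so 12. The figure of 15 can be reached but rests on unstated inputs, and nothing below depends on it. No error rate is stated for the individual comparison.

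**Inputs.** From the article: one session per condition; 10 pulses per block; one baseline block per session as divisor; two post-TMS blocks; alpha 0.05. Assumed, because not given: the pulse coefficient of variation (CV), the block-to-block drift SD on the log scale (s), and two-sided testing.

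**Divisor alone, no true effect, no drift.** To first order, for the difference between two sessions:

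- 10 post pulses: assumed variance 2 × CV²/10; true variance 2 × (CV²/10 + CV²/10). Ratio 2.
- 20 post pulses (both post blocks): assumed 2 × CV²/20; true 2 × (CV²/20 + CV²/10). Ratio 3.

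The CV cancels. By normal approximation the two-sided rates are 2 × P(Z > 1.96/√2) = 16.6% and 2 × P(Z > 1.96/√3) = 25.8%. With the t distribution on 18 df the first is 15.5%.

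**Simulation** (40,000 runs per setting, lognormal pulses, two-sample t-test on normalised pulses). The predicted direction is cathodal above sham, nominal 2.5%.

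| CV | s | 10 pulses: two-sided / directional | 20 pulses: two-sided / directional |
|---|---|---|---|
| 0.3 | 0 | 15.3% / 7.7% | 25.4% / 12.7% |
| 0.5 | 0 | 15.2% / 7.7% | 25.0% / 12.4% |
| 0.7 | 0 | 14.4% / 7.2% | 24.3% / 12.2% |
| 0.5 | 0.1 | 22.1% / 11.2% | 32.6% / 16.3% |
| 0.5 | 0.2 | 36.7% / 18.2% | 45.2% / 22.6% |

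A separate simulation with gamma pulses and CV 0.25–0.75 gave 12.7–15.4% and 23.7–25.1% two-sided without drift.

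**Two post-block means as replicates.** With block-mean variance v, the assumed variance of the difference is 2 × v/2 = v. The true variance is 2 × (v/2 + v) = 3v, on 2 df. The critical value 4.303 becomes 4.303/√3 = 2.484, and the two-sided rate is 1 − 2.484/√(2.484² + 2) = 13.1%, or about 6.5% in the predicted direction. Drift does not raise this version, because it enters numerator and denominator alike.

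**A test that counts baseline error.** A difference of differences on log pulses returns to 5% two-sided without drift. It gives 8–18% at s = 0.1 and 16–40% at s = 0.2 over CV 0.3–0.7. Only an error term at block or session level held about 5% in every setting, and one patient's data cannot supply it.

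**In patients.** If none of the 30 patients responded, the 10-pulse directional rule would label about 30 × 0.077 = 2.3 without drift, and 30 × 0.182 = 5.5 at CV 0.5 and s = 0.2. The nominal expectation is 30 × 0.025 = 0.75.

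**The case against.** The strongest reply is that the article never commits to a test across pulses. It averages the pulses, and the tests it names are group-level ANOVAs. A reader might infer that the sponsor will treat pulses as independent; the text does not say so, and the rates above are conditional on such a choice. That stands. What remains is a stated rule, not a missing detail: the article fixes an individual contrast, a significance definition and one session per condition, and no test confined to one person's data has a session-level error term under those three.

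Second, the two-sided rates overstate the error under the article's own definition, which requires agreement with sliding threshold theory and is therefore directional. That stands too, and the directional rates lead here.

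Third, a reader might infer that all later analyses inherit the label. The text does not establish this. Only the imaging contrast plainly needs a yes/no status. Consciousness level and prognosis could enter as grouping factors, and a Pearson correlation suits a continuous measure at least as well.

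Fourth, normalisation does remove a shift common to baseline and post blocks. It does not remove the error of the divisor or drift within a session. Section 2.8 itself notes that consciousness levels in these patients fluctuate, so zero drift is not a safe assumption.

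Finally, a reader might infer that the primary result is unsafe. It is not: in the group-level ANOVA participants are the replicates, and session error is part of the variation between them.

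**Conclusion.** The point holds in a limited form. The article asks for significance within a person from a design that gives a person no session-level replication. Under the ordinary tests on normalised pulses, with the divisor taken as fixed, the false label rate in the predicted direction is about 7–8% (10 pulses) or about 12% (20 pulses) against 2.5%. Two-sided it is about 13–15% and 24–25% against 5%. Using the two post-block means instead gives about 13% two-sided.

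The no-drift inflation follows from the 10-pulse baseline and the shared divisor and depends little on the assumed CV. Anything above it rests on an assumed drift, and a test that counts baseline error has no excess when drift is zero. The harm is confined to secondary and exploratory links wherever the per-patient label is used. It should be corrected, but it does not threaten the primary analysis.

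**What to change.** In section 2.11, remove the per-patient significance label and define individual retention as a continuous contrast:

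D = log(post/baseline) in the cathodal session − log(post/baseline) in the sham session,

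computed on block means, with the post measurement (POST-1, POST-2 or their mean) named in advance. Use D in the MCS/UWS and prognosis comparisons, in the correlation and in the imaging analysis, with participants as the unit of replication. Baseline error and session drift then enter as ordinary variation between participants. They weaken correlations but do not create false responders.

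Do not replace the label with a cut-off taken from the person-by-priming residual of a mixed model. With one session per condition that residual cannot separate session error from true differences in response. With half the patients assumed to be responders and an assumed cathodal effect of 3 error SDs, such a cut-off detected about 46–47% of responders, against 85% with the true error SD. It detected about 5–6% if responders also had an equal and opposite anodal effect.

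The cost is a change of wording, with no new data or patients. The downside is that no individual patient receives a yes/no status, and the imaging contrast becomes a regression on D. A defensible yes/no label would need session-level error from repeat sessions or from a reference distribution without a true effect, and the article describes neither.
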